### Local mental health service provision

Mental health services across the county are provided by one NHS mental health trust (the Cambridgeshire and Peterborough NHS Foundation Trust). Social care and third-sector organizations also offer services that support mental health. Third-sector organizations may be local charities or local branches of national or regional charities. Primary care is provided by general practices (GPs) operating in each geographical area. Primary care has recently been organized in coalitions, called primary care networks (PCNs), that enable coordination of care.

To evaluate the impact of the Peterborough Exemplar across the local area, multiple levels of care were considered. The study design includes services introduced or redesigned by the Peterborough Exemplar, such as the PCMHS and the psychological skills services (PSS), as well as existing services that may be impacted as an outcome of the Exemplar implementation, for example the Trust’s mental health adult specialist services. Fenland services included in the study design were selected by identifying corresponding services between the two areas. Table 1 presents the services that will be included in the evaluation.

**Table 1 Tab1:** Services included in the evaluation of the Peterborough Exemplar

Level of care	Service	Intervention (Peterborough)	Nonequivalent comparator (Fenland)
Primary care—physical health	General practitioners	✓	✓
Primary care—mental health	Primary care mental health service	✓	✓
Primary care—mental health	Psychological skills services Personality disorders community service Dual diagnosis service Social care pathway	✓	–
Secondary care—mental health	Adult specialist services providing mental healthcare	✓	✓
Social care	Social care pathway for specialized needs	✓	✓
Third sector	Third-sector organizations	✓	✓

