Qualitative semi-structured interviews (3) will be conducted to explore the implementation process of the Exemplar in Peterborough. Collection and analysis of qualitative data will be conducted throughout the 18-month evaluation period (see Additional file 2). Following the analysis of qualitative and quantitative data, a data triangulation plan will be generated, allowing assessment of the intervention using multiple data sources [36]. The selection of evaluation methods was also informed by exemplar programming theory, which outlined the target outcomes of the Peterborough Exemplar. The next sections detail each evaluation method.Evaluation of service user and carer outcomesRoutinely collected outcomes measures completed by service users accessing the Exemplar services and the secondary care specialist teams will be analysed pre- and post-treatment. Quality of life and care satisfaction of service users will be assessed using the DIALOG tool, an 11-item measure combining eight questions on satisfaction with quality of life and three on satisfaction with service provision [37]. A brief questionnaire with four further questions on service satisfaction and the impact of the COVID-19 pandemic is also included, as the Exemplar implementation began during the pandemic period. The EuroQol EQ-5D-5L will also measure quality of life, for use in the economic analysis of the Exemplar [38]. Finally, a brief carer-rated service satisfaction measure will be included in the evaluation to assess carers’ satisfaction with services. The carer measure has been developed within the Trust in collaboration with carers and is used to routinely evaluate carer satisfaction with provided care.Local intelligence used by the Exemplar partners to identify investment priorities highlighted service demand for PDs in particular. To assess the impact of the personality disorders community service (PDCS), the Standardized Assessment of Severity of Personality Disorder (SASPD) measure [39] will be included in the evaluation. The SASPD is completed by service users at the PDCS pre-treatment and post-treatment in both the intervention and comparator groups. The SASPD measure will be used to assess the severity level of the PDs of service users accessing the new Exemplar PD services (intervention group) and compared with the severity level of those accessing PD services in Fenland (comparator group).Measures included in the evaluation are part of clinical routine practice in both the intervention and comparator groups. A matched control approach will be adopted to compare outcomes measures between the intervention and comparator groups. In this approach, study participants between the two groups are matched based on key covariates by using, for instance, nearest-neighbour matching or weighting techniques [40]. When randomization is not possible (e.g. in a quasi-experimental design), a matched control approach allows for control of external factors that can affect the relation between an intervention and its outcome and strengthens internal validity [40, 50]. Matching between intervention and comparator groups will be based on independent variables, including age, gender, employment, ethnicity and service provided.Descriptive statistics will also be used to describe baseline characteristics of service users in the two areas. Missing responses in outcomes measures will be managed based on analytical frameworks of the selected measures (i.e. DIALOG, EQ-5D-5L and SASPD). A detailed statistical analysis plan is currently being developed to demonstrate the rationale and steps of the matched control analysis.Evaluation of service activityService activity will be analysed to assess service usage and examine differences between the intervention and comparator groups pre- and post-intervention. Specifically, routinely collected service activity data of service users who had at least one contact in a team within the Adult Specialist Directorate of the Mental Health Trust will be analysed for both geographical areas over the 18-month evaluation period. Service activity data will include demographic variables (e.g. age, gender) and service activity variables (e.g. referral source, dates of appointments, treatment team and discharge reason). Service activity data from other geographical areas or from other Trust directorates will be excluded. Aggregated data on service activity will also be obtained from Exemplar partners (social care, third-sector and primary care services). Those will include the following: (i) primary care—the number of patients seen by GPs and percentage of patients visiting the GP with a mental health need; (ii) social care—the number of new contacts and percentage of new enquiries for people with primary support reason mental health; and (iii) third sector—attendance in the peer support groups for PDs. Aggregated data will increase our understanding of service demand in the intervention and comparator groups. All quantitative data will be saved in electronic folders of the password-protected virtual work environments of the lead author and the economist researcher.Descriptive statistics will be used to present the characteristics of the patient cohort contained in service activity datasets, including percentages of demographic characteristics, services accessed by patients and diagnosis and to assess completeness of data. Changes in trends in key service utilization indicators during the 18-month evaluation period (*T*0–*T*4) between the two study groups will be analysed using *χ*^2^ (chi-square) tests. Service activity indicators include referral sources, number of contacts and access to specialist services in secondary care. Stata software (version 16) will be used to conduct the statistical analysis [41]. A detailed statistics and health economic analysis plan is currently being developed that outlines the statistical analysis of service usage.Taking into consideration data collection and analysis requirements of the selected methods and the resources available to the evaluation, assessing the Exemplar’s impact on service users focused on quantitative methods only (routine outcome measures and service activity usage). Quantitative methods allow data collection from a larger cohort of service users, are routinely collected within the Mental Health Trust and are less time-consuming for service users. However, qualitative methods, such as semi-structured interviews, can offer in-depth understanding of service users’ experience with service provision and complement quantitative findings in assessing the impact of complex interventions [24]. Collection of qualitative data from service users will be explored if the evaluation funding is extended.Evaluation of the implementation processQualitative interviewing will be used to explore individuals’ perspectives around a studied phenomenon by having an in-depth conversation [42]. Qualitative data collection will focus on three main themes: (i) the implementation of the Exemplar in Peterborough, (ii) the relationships among local service providers and (iii) the role of the patient-centred approach in the Exemplar. Semi-structured interviews are often accompanied by an interview guide to assist with focusing the discussion on selected topics [43]. Thus, an interview guide has been developed based on the three main themes of interest (see Additional file 3). Selection of interview questions was also informed by suggestions from the PPI group, professionals and the steering group coordinating the Peterborough Exemplar implementation.Purposive sampling will be used to select interview participants based on their relevance and richness of knowledge around the interview guide topics [44]. Staff members from service providers and funders participating in the implementation of the Peterborough Exemplar will be invited for an interview. Potential participants from four organizational levels will be invited: (i) frontline workers from primary care, social care and the third sector, (ii) frontline workers from secondary care, and (iii) managers and (iv) senior management staff from Exemplar stakeholder organizations. Each level includes professionals from different teams of the same organization or different organizations participating in the delivery of the Peterborough Exemplar. Interviewing key stakeholders across professional levels will allow the collection of rich and diverse information about the implementation process of the Exemplar.Focus groups could also be employed to explore professionals’ perspectives discussed in a group environment [45]. In this study, qualitative interviewing was preferred in order to reduce potential hesitancy among participants in expressing sensitive or critical views [45] in the presence of colleagues, for instance on topics about the collaboration among teams or improvements needed in the Exemplar implementation. A limitation of qualitative interviewing, however, is that topics generated from a shared understanding of participants—as can ideally happen within a focus group—may be lost [46, 47].Potential participants will be identified with the help of a gatekeeper from each Exemplar partner. A gatekeeper will indicate staff members who work in a service or team participating in the Exemplar (e.g. PDCS or PCMHS) or staff members whose work may be impacted by the Exemplar (e.g. GPs). Staff members whose work is not related to or impacted by the implementation of the Peterborough Exemplar will be excluded. Potential participants will receive an email invitation with a participant information sheet and a consent form developed by the lead author. One reminder will be sent to potential participants 2 weeks following the initial invitation. Participation in interviews will be anonymous and confidential. All interviews will be conducted via Microsoft Teams, and interviews will be recorded with an audio recorder. It is estimated that each interview will last between 45 and 60 minutes. Anonymized recordings will be transcribed verbatim, and recordings will be deleted following transcription completion.A thematic analysis will be conducted to analyse interview transcripts, a method frequently used to analyse qualitative data [48]. Thematic analysis is a method used to query a textual dataset with the aim of finding reoccurring meanings that capture topics related to the studied subject, also called “themes” [48, p. 79]. Data collection and thematic analysis will be conducted by the lead author, who has 3 years of experience on qualitative data collection and analysis, including thematic analysis. Four samples of anonymized transcripts will be discussed with GJ, KF and JP to review the coding process. GJ has received training on analysis qualitative data, and KF and JP have experience in conducting qualitative research in healthcare settings. GJ and JP’s clinical experience will also inform data analysis and interpretation. NVivo data analysis software will be used to assist with analysis of interview transcripts [49].

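### Matching on service provided has no Fenland support for at least three Peterborough-only services, and the article contradicts itself on the personality disorders service

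*Protocol article*

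**What the plan says.** The Protocol article, Methods, takes routine outcome measures from users of the Exemplar services and of the secondary care specialist teams, before and after treatment, and compares the areas by a matched control approach. The matching set is given in one sentence: "Matching between intervention and comparator groups will be based on independent variables, including age, gender, employment, ethnicity and service provided". The technique is given only by example, "by using, for instance, nearest-neighbour matching or weighting techniques", and the detail is left to a later document: "A detailed statistical analysis plan is currently being developed to demonstrate the rationale and steps of the matched control analysis".

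Table 1, in the section on local mental health service provision, has a primary-care mental health row reading "Psychological skills services Personality disorders community service Dual diagnosis service Social care pathway", with a tick for Peterborough and a dash for Fenland. The text before the table says: "Fenland services included in the study design were selected by identifying corresponding services between the two areas".

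On the personality disorders service, Methods states: "The SASPD is completed by service users at the PDCS pre-treatment and post-treatment in both the intervention and comparator groups". It adds that severity among users of the new service will be "compared with the severity level of those accessing PD services in Fenland (comparator group").

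**The concern.** Matching needs every value of a matching variable to occur in both groups. Here the article names a variable and, in Table 1, shows values of it that exist in one group only. The people concerned are not marginal: they use the services the Exemplar created, and Methods places them in the outcome analysis.

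There is a second difficulty. Creating new services is the second pillar of the Exemplar and the first item in its composition under Design. Which service a person receives is therefore partly a result of the intervention and not a characteristic that precedes it.

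At stake is objective (i), the effect on quality of life and satisfaction, whose results go to commissioners and NHS England. A matched estimate confined to shared services, or built partly on cross-service pairs, could be read as the effect of the whole Exemplar while giving no valid controlled evidence on the services without overlap.

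**Working it through.** The article gives no sample size and no user count per service, so there is no stated figure to reproduce. The check is of common support, followed by an illustration under stated assumptions.

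**1. Count from Table 1.** Nine services are named. Five are ticked in both areas: general practitioners, PCMHS, adult specialist services, social care pathway for specialised needs, and third-sector organisations. Four are ticked in Peterborough only: psychological skills, PDCS, dual diagnosis and the primary-care social care pathway. 5 + 4 = 9. Within primary-care mental health, 4 of 5 services are Peterborough only; the exception is the PCMHS.

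**2. Set Table 1 beside Methods for the PDCS.** Table 1 has a dash for Fenland. Methods has the severity measure completed at the PDCS in both groups and names users of Fenland personality disorder services as the comparator. Both cannot stand as written. If Methods is right, 4 − 1 = 3 services lack a counterpart; if Table 1 is right, 4 do.

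**3. What each technique does.** Let k be a service with no Fenland users.
- Exact matching, trimming, or a caliper tight enough to enforce service: no Fenland user has value k, so all its users are lost.
- Nearest-neighbour matching without a caliper: nobody is lost, but every user of k is paired with someone from another service.
- Weighting: the weighted Fenland share of k is Σwᵢ·1(Sᵢ = k) / Σwᵢ = 0 for any weights, while the Peterborough share is above 0, so no weights balance it. A propensity score that includes service is n/(n + 0) = 1 for these users.

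**4. Size, by assumption.** Let s be the share of Peterborough outcome records from the four services, spread evenly over them. The share lost or mismatched is s if Table 1 is taken literally, and (3/4)s if the Fenland personality disorder comparator is accepted.

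| Assumed s | Table 1 literal | PD comparator accepted |
|---|---|---|
| 10% | 10% | 0.75 × 10% = 7.5% |
| 30% | 30% | 0.75 × 30% = 22.5% |
| 50% | 50% | 0.75 × 50% = 37.5% |

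A simulation with an assumed 600 Peterborough and 300 Fenland users agreed under exact matching: 9.5%, 29.5% and 50.8% in the first case, and 7.7%, 21.8% and 38.7% in the second. Nearest-neighbour matching without a caliper dropped nobody. Instead it mismatched all users of the four services on service in the first case, and 74% to 81% of them in the second.

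**5. Service as part of the intervention.** If the Exemplar moves some people into psychological skills or dual diagnosis services, those left in the Peterborough PCMHS may differ from Fenland PCMHS users, who had no such route. Pairing PCMHS with PCMHS then compares groups partly formed by the intervention, and leaves out any benefit of being moved.

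**The case against.** The strongest reply is that the analysis plan is not shown and the steps are expressly deferred to it. Service provided could there be coded by level of care or by corresponding service, in line with how Fenland services were selected. Under such coding a psychological skills user might be matched to a Fenland PCMHS user, and support would exist. It is fair that the coding, the algorithm and the handling of unmatched users belong in that plan, and their absence here is no fault. But the article itself fixes the variable, and its wording allows further variables without removing this one. As Table 1 labels the services, three have no counterpart. Coding by level of care would still condition on where the Exemplar places people.

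Stronger readings are tempting and are not supported:
- A reader might infer that all users of the new services drop out. That follows only under exact matching, trimming or a tight caliper, none of which the article names.
- A reader might infer that all four services lack controls. Methods describes a Fenland comparator for personality disorders, so for the PDCS the document shows a contradiction and not an established absence.
- A reader might infer that nothing of the Exemplar can be compared. The PCMHS is among the services it introduced or redesigned and is ticked in both areas.
- A reader might take the resident populations of 184 000 and 95 000 and conclude that 1 − 95/184 = 48% of Peterborough users go unmatched. That needs equal contact rates and 1:1 matching without replacement, neither of which is stated, and it has no bearing on this defect.

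**Conclusion.** The point holds in a limited form. With services as labelled in Table 1, service provided has no common support for psychological skills, dual diagnosis and the primary-care social care pathway. Their users will be lost, paired across services or left unbalanced, according to the technique chosen. For the PDCS, Table 1 and Methods conflict and must be reconciled before anyone can say whether controls exist. Independently of overlap, the variable is a poor choice because the Exemplar changes which service people receive.

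Comparisons within the PCMHS and the adult specialist teams remain possible, subject to the case-mix caution in step 5. The share of users affected cannot be derived from the article; the 7.5% to 50% range above rests entirely on assumed shares and an even spread over services. That the matched result would be presented as the effect of the whole Exemplar is a risk and not something the article states; the Discussion promises a description of both groups and of the analysis at publication.

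**What to change.** Replace service provided in the matching set with characteristics fixed before service allocation: diagnosis or presenting need, and the pre-treatment DIALOG, EQ-5D-5L or SASPD score as applicable, with the age, gender, employment and ethnicity already listed. Do not use referral source: Methods lists it among the activity indicators to be compared between areas, so it is itself an outcome.

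Reconcile Table 1 with Methods on whether Fenland has a personality disorders service that supplies SASPD data, and name it. Report overlap for each service. Limit the matched estimate to services with overlap, say so beside it, and present any service without Fenland overlap as an uncontrolled pre-post result.

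The cost is wording in a plan still being written, plus one correction to Table 1 or the text. There are two real downsides. The analysis will rely on routine diagnosis coding. And because the new services have lower access thresholds, Fenland people with the same need may be in no service and have no outcome record, so some users of the new services may still have no control.

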**Methods:**

A quasi-experimental design with an intervention group and a nonequivalent comparator group has been developed to compare service provision provided in Peterborough pre- and post-intervention with services provided in Fenland, a neighbouring area where service users access usual care. Two evaluation methods will be employed to compare service provision between the two groups: (1) outcome measures completed by service users and carers will be analysed to assess quality of life and service satisfaction, and (2) service activity data will be analysed to assess service usage. In addition, qualitative interviews will be conducted with staff members of participating organizations to explore the implementation of the Exemplar in Peterborough and evaluate knowledge exchange processes among local service providers. A matched control approach will be used to compare outcome measures between the two areas. Descriptive and inferential statistics, including chi-square tests, will be used to analyse service activity data and examine differences between the two areas. A thematic analysis will be adopted to analyse qualitative data.

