## Methods

Three methods will be employed to assess the impact of the Peterborough Exemplar on service provision as well as the implementation process of the intervention. Specifically, two methods will be adopted as part of a quasi-experimental design comparing service provision in Peterborough and in Fenland. Routine outcome measures (1) will be analysed to assess quality of life and service experience of service users and carers. Routine service activity data (2) will be analysed to evaluate service utilization. Analysis of outcome data and service activity will be based on a comparison between the intervention and comparator groups pre- and post-intervention, namely a period of 18 months (October 2020–March 2022). Data will be collected in four time periods: *T*0 (October 2020–baseline), *T*1 (April 2021), *T*2 (October 2021) and *T*3 (April 2022). In addition to the final analysis, data will be analysed at the end of each period to assess the impact of the Exemplar and inform its delivery (see Additional file 2).

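### The chi-square tests named for service activity do not fix a test of the difference in change between Peterborough and Fenland, and on contact counts their p-values may be invalid

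*Protocol article*

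**What the plan says.** In the Methods section of the protocol article, under the evaluation of service activity, the aim is to "examine differences between the intervention and comparator groups pre- and post-intervention". The quantity to be tested is described as "Changes in trends in key service utilization indicators during the 18-month evaluation period", compared between the two study groups. The only inferential method named there is chi-square, and the indicators follow directly: "chi-square) tests. Service activity indicators include referral sources, number of contacts and access to specialist services in secondary care".

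The data are "routinely collected service activity data of service users who had at least one contact in a team within the Adult Specialist Directorate", and they carry "service activity variables (e.g. referral source, dates of appointments, treatment team and discharge reason". One person can therefore contribute many dated contacts. The same section says "Data will be collected in four time periods" (T0 to T3).

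The abstract is looser: "Descriptive and inferential statistics, including chi-square tests, will be used to analyse service activity data and examine differences between the two areas". The Methods section adds that a fuller statistical and health economic plan for service usage is being written. Matching is described for the outcome measures only. The Design section calls the comparator nonequivalent.

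**The concern.** The stated aim is a difference in change: did an indicator move differently in Peterborough than in Fenland? That is an area-by-period interaction. A reader who follows the article could run any of three chi-square tests:

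- **Area by category at one time point.** This tests a gap at that time. A nonequivalent comparator may show such a gap before anything is introduced.
- **Period by category within Peterborough.** This tests change in one area and makes no use of Fenland. A shift common to both areas, for instance one driven by the pandemic, would count as an effect.
- **Area by period on counts of contacts.** This does compare relative change, but it treats every contact as an independent observation, although contacts are nested in patients.

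Results are to be analysed after each period to inform delivery, and they go to commissioners and NHS England. A static gap, a common trend or clustering of contacts could be reported as an effect of the Exemplar. None of the three tests gives the size of the difference in change or its uncertainty.

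**Working it through.** The article gives no sample size, rate, variance or effect size for service activity, so there is no figure to reproduce. Every input below is an assumption except the population ratio, from the Study setting section: 184 000 / 95 000 = 1.94. It is used only to set group sizes of 1,937 and 1,000 patients. Nominal two-sided alpha is 0.05.

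**1. Binary indicator, identical change in both areas.** The log-odds rise by 0.3 in each area, so there is no difference in change. Fenland starts at 20% and moves to 25.2%. Peterborough starts at 20%, 22% or 25% and moves to 25.2%, 27.6% or 31.0%. Observations are independent, and 2,000 datasets were simulated per case. Rejection rates:

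| Peterborough baseline | Post-period area x access | Peterborough pre/post | Area x period interaction |
|---|---|---|---|
| 20% | 6% | 98% | 5% |
| 22% | 28% | 99% | 5% |
| 25% | 90% | 99% | 5% |

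Hand check of the post-period test at 25%: difference 0.0580; pooled proportion 0.2906; SE = sqrt(0.2906 x 0.7094 x (1/1937 + 1/1000)) = 0.0177; z = 3.28; power = Phi(3.28 - 1.96) = 0.91. At 22%: difference 0.0234, SE 0.0172, z = 1.36, power 0.27.

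Hand check of the pre/post test at 20%: difference 0.0523; pooled proportion 0.2262; SE = sqrt(0.2262 x 0.7738 x 2/1937) = 0.0134; z = 3.89; power = Phi(3.89 - 1.96) = 0.97. That column is best read as 97% to 99%.

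**2. Contact counts, area x 4-period Pearson chi-square, same time pattern in both areas** (1,000 datasets per case). Degrees of freedom are (2 - 1)(4 - 1) = 3, and the critical value is 7.815. If contacts per patient-period have mean m and gamma variation with shape k drawn afresh each period, the variance-to-mean ratio is D = 1 + m/k. The rejection rate is then approximately P(chi-square on 3 df > 7.815/D).

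| m | k | D | Formula | Simulated |
|---|---|---|---|---|
| 2 | 1 | 3 | 46% | 44% |
| 5 | 1 | 6 | 73% | 74% |
| 10 | 1 | 11 | 87% | 84% |
| 2 | 2 | 2 | 27% | 29% |
| 5 | 2 | 3.5 | 53% | 52% |
| 10 | 2 | 6 | 73% | 72% |

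Two contrasts use the same table. With pure Poisson contacts it rejects 4% to 6% of the time. If patients differ only by a constant personal rate, with Poisson variation over time, it also rejects 4% to 6%: given each patient's rate, contacts spread over the periods in the same proportions in both areas. Inflation therefore needs variation within patients over time beyond Poisson.

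**3. Recurring patients, binary indicator.** If the same patients are seen in both periods (assumed patient SD 2.0 on the logit scale) and the interaction test ignores this, it rejects 0.7% to 1.7% of the time. Here the error is conservative.

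**The case against.** The strongest reply is that the article does not say which table will be tested or what a row is. It defines the dataset by service users, not contacts. One record per patient per period would have no repeated-contact problem within a period, and referral source and specialist access can naturally be counted per referral or per patient. The abstract presents chi-square as one among other inferential methods, and detail is deferred to a plan not shown. The Study setting section promises that population differences will be considered at analysis, and a constant population ratio does not disturb an area-by-period homogeneity test in any case.

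Much of this stands, and it limits what can be claimed. A reader might infer that a chi-square test can never address a difference in change, or that the reported p-values are bound to be wrong. The documents support neither. An area-by-period chi-square on counts tests relative change when denominators are stable, and a Wald test of an interaction is itself a chi-square. The static-gap problem and the inflated error on contacts also arise from different tables, so they should not be added together.

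The reply does not remove the point. The Methods section commits to chi-square for trends between groups and lists a per-patient count among the indicators. A later plan can add detail, but if it only elaborates that choice it inherits the weakness, and if it replaces the choice it departs from the article.

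**Conclusion.** The point holds as a mismatch between the stated question and the stated test. Two of the three plausible chi-square tests do not address the difference in change. The third does, but its validity for contacts depends on an independence assumption that routine contact data may well break. None yields an effect estimate with an interval.

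The size cannot be fixed from the documents. Under the assumed inputs, false positives for contacts run from about 5% (constant patient rates) to about 30% to 85% (overdispersion within patients over time). A post-period test rejects at 28% or 90% when baselines differ by 2 or 5 percentage points and both areas change alike. For binary indicators on recurring patients the error can run the other way. These figures show direction and sensitivity; they do not predict this evaluation's error rates.

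**What to change.** For each indicator, replace the chi-square test of trends with a regression containing area, period and area x period, plus the demographics already in the service activity data (age and gender are named):

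- **Access to specialist services:** logistic regression.
- **Referral source:** multinomial logistic regression.
- **Number of contacts:** negative binomial regression, with a log person-time offset for patient-level rows or a log population offset for aggregated area-period counts.

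Use patient-clustered standard errors for patient-level data, and report the area x period ratio with its 95% CI as the result. For aggregated counts, 2 areas x 4 periods give 8 cells and the interaction model has 8 parameters, so overdispersion cannot be estimated at that level. Use finer time intervals or report those counts descriptively. Keep chi-square for describing baseline characteristics. Name the unit of analysis, and reconcile the period labels, since the service-activity text runs to T4 while only T0 to T3 are defined.

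State also that with one area per group, no model separates area-specific shocks from the intervention; patient-clustered errors do not cover this.

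The cost is revised wording and a few more models on the same routine data, in the Stata software already named. For contacts the intervals will probably be wider than a chi-square analysis would imply.
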